### Rationale and reinforcement schedule for monthly A-CRA competency

In addition to reinforcing exposure to a threshold number of procedures, we believed it was important to reinforce the quality of delivery (*i.e.*, competence). Thus, P4P therapists also are provided the opportunity to earn a $50 bonus for each month that a randomly selected session recording has at least one core procedure rated at or above the minimum level of competence required for certification. Importantly, in order to ensure a representative sample of session recordings, only those therapists who submit at least 80% or more of treatment session recordings are eligible to have a session rated for competence. Because it would take approximately three months after randomization before P4P participants would be eligible to begin receiving their first bonus associated with delivery of Target A-CRA, reinforcing Monthly A-CRA competency is important as it can be reinforced sooner and more frequently.

### Recruitment

The initial recruitment period for the study occurred between November 2008 and February 2009 and was limited to the sites and therapists participating in CSAT's AAFT initiative. Since the two cohorts of AAFT were funded in different years, recruitment of the study sites was in months 27 and 15 of the cohorts' respective 36-month grants. Although the site's therapists were the target population for the RTP, it was necessary to first obtain permission from each grantee's principal investigator (PI) and/or treatment agency director.

### Site recruitment

Recruitment of study sites began in November 2008. AAFT grantees were first introduced to the study via an email briefly explaining the goals of the study and the extent of involvement the study would require. Email attachments included: the memorandum of understanding, which outlined the responsibilities of the study sites, the informed consent, which outlined the responsibilities of the therapist participants, and a signed letter of support from the CSAT project officer. The study PI ([name]) followed up the e-mail introductions with telephone calls with each site PI to answer questions and inquire about the site's willingness to participate in the study. Out of the 34 grantees, two were excluded for study participation because they were not providing services in an outpatient setting, and two were ineligible because they could not be matched to a comparable site for randomization. Of the 30 eligible grantees, 29 (97%) agreed to participate by returning signed copies of the memorandum of understanding.

### Staff recruitment

Recruitment of therapist participants for the study began one month after site recruitment. In order to be eligible to participate in the study, therapists had to work at one of the participating AAFT grantee sites and be delivering A-CRA or ACC to adolescents. Study packets containing a cover letter, informed consent, staff survey, and a W-9 tax form were mailed to 92 eligible therapists. Of these, 82 (89%) agreed to participate.

### Randomization

Although random assignment of therapists might appear ideal, a number of issues made such an approach impractical and led to the decision to randomize in clusters by site. For example, dividing small (two- to four-person) clinical teams within a site through random assignment may lead to unintended consequences due to some therapists being eligible for incentives and others not. For example, the IAU group might work harder than they normally would to achieve goals (*i.e.*, compensatory rivalry), which would threaten the study's internal validity (increasing type 2 error probability). Another possibility is that this situation would lead to resentful demoralization of therapists in the control group, and they would deliver sub-par effort (increasing type 1 error probability). In order to avoid these potential problems, we used an adaptive randomization procedure referred to as urn randomization [71,72] to assign sites to the two study conditions. Shadish, Cook, and Campbell [71] recommend using such adaptive procedures whenever feasible and when good matching variables can be found, and have noted that the best matching variables are pre-test scores on the outcomes of interest.

Given the two cohorts of AAFT grantees were in months 27 and 15 of their respective 36-month grants, pre-test data was available on several important matching variables. Using existing project data on therapists performance and from staff questionnaires (described further below), we created several grantee-level measures including: average Target A-CRA rate; average DSR upload rate; three-month client recovery rate; percentage of Caucasian clients; percentage of Hispanic clients; percentage of male clients; number of therapists; average therapist age; percentage of Caucasian therapists; percentage of male therapists; and AAFT staff ratings of expected performance. This last measure was used to take into account any recent changes (*e.g.*, turnover of supervisor, major improvement/decrements in performance) that might impact performance in the study, and was based upon independent rankings from the director and coordinator of the AAFT training team. Both raters agreed on the rankings for all but two study sites (Kappa = 0.86), and the two raters were able to discuss and resolve these two inconsistencies. Each of the above-mentioned existing measures was then entered by AAFT cohort into an urn randomization software program called gRand.

Although urn randomization was conducted at the site level, it resulted in a balanced distribution of therapists into the two study conditions (See Table 1). Of the 82 therapists used to randomize sites most were female (74.4%) and Caucasian (56.1%). They had an average age of 37 years (SD = 11.6). In terms of their education and work experience, most had either a Masters (52.4%) or a Bachelor's (41.5%) degree, with an average of 4.3 years of substance abuse counseling experience. Seven percent reported personally being in recovery for alcohol or other drugs. Based on therapist self-report, the average achievement of Target A-CRA implementation prior to the experiment was 19.2%, and the average session recording rate of fidelity was 41.0%. Based on three-month post-intake follow-up data prior to the experiment, the average percentage of therapists' adolescent clients in recovery was 45.9%. Notification to sites and individual participants about the official commencement of the study and their assignment to either the IAU or P4P conditions were sent via email on 16 January 2009 for the AAFT-1 and on 13 February 2009 for AAFT-2.

**Table 1 T1:** Baseline characteristics of therapists at randomization

	P4P (n = 42)	IAU (n = 40)	Overall (N = 82)
	% or M (SD)	% or M (SD)	% or M (SD)
**Age**	36.7 (11.3)	36.7 (12.2)	36.7 (11.6)
			
**Race**			
American Indian/Alaska Native	2.4%	2.5%	2.4%
Asian	0.0%	5.0%	2.4%
African American	11.9%	17.5%	19.5%
Caucasian	52.4%	60.0%	56.1%
Hispanic/Latino	31.0%	15.0%	23.2%
Other	2.4%	0.0%	1.2%
			
**Gender**			
Male	19%	32.5%	25.6%
Female	81%	67.5%	74.4%
			
**Education**			
Less than Bachelor's Degree	0.0%	7.5%	3.7%
Bachelor's Degree	47.6%	35.0%	41.5%
Master's Degree	50.0%	55.0%	52.4%
Doctoral Degree	2.4%	2.5%	2.4%
			
**Years of SAT Experience**	3.3 (3.3)	5.4 (7.1)	4.3 (5.6)
			
**Self-reported being in recovery**	7.1%	7.5%	7.0%
			
**Pre-RTP Target A-CRA Rate**	21.4%	16.7%	19.2%
			
**Pre-RTP Session Recording Rate**	40.4%	41.7%	41.0%
			
**Pre-RTP 3-month Client Recovery Rate**	46.5%	45.1%	45.9%

Note: No statistically significant differences between conditions

### Study measurements

Given that the primary aims of the study were to examine the effectiveness and CE of providing monetary incentives to therapists as a method to improve treatment implementation and subsequent outcomes for adolescents and their caregivers, it was necessary to collect measures from multiple levels (*i.e.*, therapist, adolescent, and grantee) and over several different time points.

### Therapist background and attitude measures

As noted previously, all study participants completed a staff survey at the time of consenting to participate. This 15-page survey took approximate 30 to 45 minutes and asked questions about the individual and the therapist's work environment. Examples include basic socio-demographic characteristics such as age, race, and gender; highest educational degree obtained; and years of substance abuse counseling experience. The survey also included the Minnesota Satisfaction Questionnaire (MSQ) [73], the Pay Satisfaction Questionnaire (PSQ) [74], several scales from the Organizational Readiness for Change (ORC) instrument [75], and several measures adapted from the Provider Attitudes toward Incentive (PAI) [61] instrument. Assessment of changes in participants' attitudes and work environments was measured via three-month follow-up versions of the survey.

### Therapist implementation measures

The two implementation measures being reinforced as part of the study are Target A-CRA and Monthly A-CRA Competency. Developed using existing AAFT data, Target A-CRA is a dichotomous (1 = yes, 0 = no) measure. It is defined as the delivery of 10 or more of the following 12 A-CRA procedures: functional analysis of substance using behavior; functional analysis of prosocial behavior; happiness scale; treatment plan/goals of counseling; communication skills; problem solving skills; adolescent-caregiver relationship skills; caregiver overview, rapport building, and motivation; homework reviewed; drink/drug refusal skills; relapse prevention; and increasing prosocial recreation during the first 14 weeks of an adolescent's AAFT treatment experience (but in no fewer than seven sessions). See the A-CRA treatment manual for a description of these A-CRA procedures [76]. Additionally, because identifying, discussing, and reviewing the adolescent's reinforcers is considered a central mechanism of change within the A-CRA philosophy, as part of Target A-CRA, therapists also must demonstrate one of these three components in at least 50% or more of the sessions conducted during this time period. Therapist-reported data on more than 450 adolescents uploaded to AAFT's implementation tracking system (*i.e.*, https://www.EBTx.org) indicated adolescents who received Target A-CRA had significantly (*p *< 0.05) greater reductions in days abstinent at both three- and six- month post-intake assessments. Importantly, although therapist reports are used to identify adolescents who appear to have received Target A-CRA, official achievement of Target A-CRA for the study requires independent verification (via listening to DSR) by a trained A-CRA rater. See Garner, Barnes, and Godley [77] for complete details regarding the training process for A-CRA raters.

Monthly A-CRA Competency is a dichotomous (1 = yes, 0 = no) measure and indicates whether or not a randomly selected session recording was rated at or above the minimum level of competence required for A-CRA certification (*i.e.*, rating of 3 or higher on all components of the procedure). As described in the A-CRA coding manual [78], each component of an attempted A-CRA procedure is rated using the following categories: 1 = poor, 2 = needs improvement, 3 = satisfactory, 4 = very good, and 5 = excellent. To ensure a representative sample of session recordings, only those therapist participants who submitted at least 80% or more of treatment sessions (minimum of five sessions per month) are eligible to have a session randomly selected and rated for competence. This requirement was implemented in order to reduce the risk of therapists trying to manipulate the criterion being reinforced by only uploading those sessions they expected would pass the competency rating.

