### Rationale and reinforcement schedule for target A-CRA

Research has suggested that the degree of implementation can be as important as the efficacy of the EBT, with the biggest effects coming from well-implemented, highly efficacious interventions [30]. Similarly, our prior research [65] has shown that adolescents who received a threshold exposure of A-CRA were significantly more likely to be in recovery at follow-up. Increasing the number of adolescents who receive Target A-CRA would be expected to result in a higher likelihood that adolescents would have more positive treatment outcomes. Thus, one of the questions the study was designed to examine is the extent to which monetary bonuses could increase the probability that an adolescent receives Target A-CRA. As part of the RTP, study therapists in the P4P condition receive a $200 bonus for each adolescent who receives Target A-CRA within the first 14 weeks of AAFT and in no fewer than seven A-CRA sessions. In order to attribute improvements in adolescent outcomes to the incentives, only outcome data from adolescents admitted to the AAFT project after sites were randomly assigned to the study conditions will be used in Target A-CRA-related analyses.

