### Analytic plan

#### Effectiveness-related analyses

Because of the multilevel nature of the data, Hierarchical Linear Modeling (HLM) [85], which is able to handle this type of data by allowing the relationship between the variables of interest to vary by higher-level groupings (*i.e.*, therapists and/or sites), will be used to analyze the effectiveness-related hypotheses. For H1.1 (*i.e.*, Target A-CRA is more likely for adolescents in the P4P group), the main independent variable is group assignment (IAU versus P4P), and the dependent variable is whether adolescents received Target A-CRA. Adolescents are at level one, therapists are at level two, and sites are at level three. For Hypothesis H1.2 (*i.e.*, Monthly A-CRA Competence is more likely for therapists in the P4P group), the main independent variable is group assignment (IAU versus P4P), and the dependent variable is the percentage of months therapists demonstrated A-CRA competence. Here, therapists are at the lowest level (*i.e.*, level one), and sites are at the next highest level (*i.e.*, level two). For Hypothesis H1.3 (*i.e.*, being in recovery after intake is more likely for adolescents in the P4P group), the main independent variable is group assignment (IAU versus P4P), and the dependent variable is whether adolescents are in recovery post-intake. Again, adolescents are at level one, therapists are at level two, and sites are at level three.

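### H1.1 counts Target A-CRA only when it is reported and then verified on recordings; only P4P pays for that, so part of any P4P advantage could be better documentation

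*Protocol article*

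**What the plan says.** All references are to the protocol article.

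- **Outcome of H1.1** (Effectiveness-related analyses). The hypothesis is that "Target A-CRA is more likely for adolescents in the P4P group", and "the dependent variable is whether adolescents received Target A-CRA". Adolescents are level one, therapists level two, sites level three.
- **Scoring** (Therapist implementation measures). "Target A-CRA is a dichotomous (1 = yes, 0 = no) measure". No third state for cases that cannot be assessed is described.
- **How a case is established** (same section). First, "therapist reports are used to identify adolescents who appear to have received Target A-CRA". Then "official achievement of Target A-CRA for the study requires independent verification (via listening to DSR) by a trained A-CRA rater". The words *for the study* make this the study definition as well as a payment check.
- **Incentives.** Under Rationale and reinforcement schedule for target A-CRA, "study therapists in the P4P condition receive a $200 bonus for each adolescent who receives Target A-CRA". The section on monthly competency adds a $50 bonus, also for P4P only. To have a session rated, a therapist must have submitted at least 80% of session recordings.
- **Both arms are asked to document.** Overview of RTP study design lists session reports and matching recordings as part of the training model for both groups.
- **State before the trial** (Randomization and Table 1). "the average session recording rate of fidelity was 41.0" per cent: 40.4% in P4P and 41.7% in IAU. Upload rate was one of the site measures entered into the urn randomization.

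**The concern.** Verification from recordings removes false positives: a therapist cannot earn a 1 by over-reporting. It does nothing about false negatives, meaning adolescents who received the threshold treatment but whose sessions were not reported or not recorded well enough to confirm it. If that loss were the same in both arms, the rates would be understated but the odds ratio would stay near 1 under no effect. Here the loss can differ, because the intervention attaches money to the documentation on which the outcome depends. Reporting and recording are then affected by treatment and also decide whether the outcome can be counted.

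At stake is what H1.1 can be said to show. The trial asks whether incentives lead more adolescents to receive the threshold treatment. A difference in the verified count could instead show that incentives lead therapists to upload more of what they already deliver. The same difference is the denominator Q for cost per adolescent receiving Target A-CRA (Cost effectiveness-related analyses), so any inflation there makes P4P look cheaper per case.

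The article recognises selective uploading as a threat to Monthly A-CRA Competency and sets the 80% rule against it. It describes no counterpart for Target A-CRA.

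**Working it through.** **Inputs from the article.** Pre-trial recording rate 41.0% (P4P 40.4%, IAU 41.7%); pre-trial Target A-CRA rate 19.2% (P4P 21.4%, IAU 16.7%); 42 P4P and 40 IAU therapists; 80% eligibility level for the $50 bonus.

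**Reproducing the stated figures.**
- Recording: (42 × 40.4 + 40 × 41.7) / 82 = 41.03%, stated as 41.0%.
- Target A-CRA: (42 × 21.4 + 40 × 16.7) / 82 = 19.11%, stated as 19.2%; the gap is within the rounding of the arm values.

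**Assumptions.** True delivery is 19.2% in both arms, so there is no real effect; this figure is used only as a plausible level. Unverifiable cases score 0. The share of true cases that can be verified equals the session recording rate. IAU stays at 41%. P4P's rate after randomization is unknown and is varied.

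**Formula.** Observed rate = true rate × verifiable share.

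| Verifiable share, IAU v P4P | Observed IAU | Observed P4P | Difference (points) | Ratio |
|---|---|---|---|---|
| 41% v 41% | 7.9% | 7.9% | 0 | 1.00 |
| 41% v 60% | 7.9% | 11.5% | 3.6 | 1.46 |
| 60% v 80% | 11.5% | 15.4% | 3.8 | 1.33 |
| 41% v 80% | 7.9% | 15.4% | 7.5 | 1.95 |
| 41% v 100% | 7.9% | 19.2% | 11.3 | 2.44 |
| 80% v 80% | 15.4% | 15.4% | 0 | 1.00 |

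For example, 0.192 × 0.41 = 0.0787 and 0.192 × 0.80 = 0.1536; the odds ratio is (0.1536 / 0.8464) / (0.0787 / 0.9213) = 2.12. For 41% v 60%, 0.192 × 0.19 = 0.03648.

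**Direction.** The ratio is inflated whenever P4P cases are more often verifiable. The absolute difference is not always inflated. At 41% v 80%, with true P4P delivery p, observed minus true difference is (0.80p − 0.0787) − (p − 0.192) = 0.1133 − 0.20p, which is positive while p is below about 0.57.

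**Sensitivity to the number of recordings needed.** The article does not give this number. Assume 12 sessions, each recorded independently with probability 41% v 80%:
- 4 recordings needed: verifiable share 79.5% v about 100%; 19.2% appears as 15.3% v 19.2%, a difference of 3.9 points.
- 5 recordings needed: 59.0% v 99.9%; 11.3% v 19.2%, a difference of 7.9 points.

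**What bounding would show.** In the 41% v 80% row, if every delivered case is reported, the unverifiable cases are 19.2 − 7.9 = 11.3 points in IAU and 19.2 − 15.4 = 3.8 points in P4P. Counted all-no, the difference is +7.5. Counted all-yes, it is 0. In the worst case for P4P (IAU yes, P4P no), it is 15.4 − 19.2 = −3.8. The bounds contain the true value of 0; the verified analysis alone does not reveal the problem.

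**The case against.** **The zero score is inferred.** The article says achievement requires verification. It does not say how H1.1 treats a reported case that cannot be verified, and a condensed article may leave that to the full protocol or SAP. This stands as a limit on certainty. The article does, however, fix a two-step definition on a 1/0 scale, and under it such a case has no route to 1.

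**Both arms must document, and upload rate was balanced.** Both are true, and IAU therapists also have non-financial reasons to upload, through certification feedback and fidelity checks. But about 41% was the rate achieved under that same expectation, and the incentives act after the randomization that balanced it. How far the arms then diverge is unknown.

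**Verification is a strength.** It is, particularly where each case earns $200, and it should stay.

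**Stronger readings that a reader might infer.**
- *That P4P therapists are paid to upload 80% of recordings.* They are paid for a competent month; 80% is a condition of eligibility. It gives a reason to record, but nothing shows that they reach it.
- *That seven recordings are needed to verify a case,* which would give much larger distortions. Seven is the minimum number of sessions delivered; the article sets no number of recordings.
- *That the self-reported 19.2% is wrongly set against the verified trial outcome.* The article makes no such comparison. Pre-test data serve site matching and baseline description, and H1.1 compares the arms.

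**Conclusion.** The concern holds as a risk of differential outcome ascertainment. As the article defines Target A-CRA, H1.1 and its cost per case could favour P4P without any difference in delivery. The documents do not show that the effect is inflated, because that requires P4P to record or report more than IAU after randomization, and those rates are not given.

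Under equal true delivery of 19.2% and simple scaling, the artefact runs from 0 (equal recording) through 3.6 points (41% v 60%) to 7.5 points (41% v 80%), a ratio of up to 1.95 over that range. It rests on three assumptions: unverifiable cases score 0, verifiability tracks the recording rate, and IAU stays near its pre-trial level. The mechanism and direction come from the text; the size does not.

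**What to change.** 1. Keep recording-verified Target A-CRA as the main H1.1 outcome and as the payment rule.
2. Report by arm the recording completeness and the number of adolescents reported as achieving the target but not verifiable.
3. Rerun H1.1 and cost per adolescent receiving Target A-CRA with those adolescents counted all-yes and all-no, and in the worst case for P4P (IAU yes, P4P no).
4. Show therapist-reported Target A-CRA in both arms as a secondary sensitivity analysis, noting that payment may inflate P4P reports.
5. Label any analysis restricted to verifiable cases as conditioning on a post-randomization variable that the incentive may change.
6. If the result depends on how unverifiable cases are handled, conclude an effect on documented delivery only.

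The bounds do not cover delivery that was never reported; the text should say so.

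The cost is a few extra tabulations and model runs on tracking data already collected, with no new ratings, and possibly a more cautious claim.

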### Adolescent intake and follow-up measures

In addition to examining the extent to which monetary incentives improve treatment implementation (*i.e.*, delivery of Target A-CRA, demonstration of Monthly A-CRA Competency), a third aim of the RTP study is to examine the extent to which these two implementation measures impacted treatment outcome for the adolescent clients. Being 'in recovery' (*i.e.*, no past month alcohol or other drug use, abuse, or dependence symptoms while living in the community) was selected as the primary outcome of interest, as is consistent with the primary clinical outcome used in the Cannabis Youth Treatment (CYT) study [8]. Intake and follow-up versions of this measure were collected using the GAIN [79], which is a comprehensive biopsychosocial assessment designed to integrate research and clinical assessment into one structured interview. The GAIN's main scales have been shown to demonstrate good internal consistency (alpha greater than 0.90 on main scales, 0.70 on subscales), test-retest reliability (Rho greater than 0.70 on days/problem counts, kappa greater than 0.60 on categorical measures), and to be highly correlated with measures of use based on timeline follow-back methods, urine tests, collateral reports, treatment records, and blind psychiatric diagnoses (rho of 0.70 or more, kappa of 0.60 or more) [79-81]. GAIN data were collected as part of the AAFT project's evaluation and were de-identified prior to being used as part of the RTP study. In order to access this data, the study group sought and received a signed data sharing agreement from each site that explicitly allowed the use of the de-identified adolescent data for the purposes of research, public health, or healthcare operations.

